### Statistical analysis plan

Data will be explored, cleaned and analysedusing STATA version 16.0 [56]. Descriptive statistics will be used to describe the demographic and clinical characteristics of the participants. The distribution of the continuous data will be assessed using skewness, kurtosis as well as histogram. Continuous data will be presented as mean and standard deviation if the data is normally distributed, otherwise median and interquartile range. Categorical variables will be presented as frequency and percentage.

#### Prognostic factors that influence the rehabilitation outcomes

Linear regression modelling will be used to investigate the factors that influence the knee function of the patients. Simple linear regression will be used to explore the variables which significantly predict the outcome, and stepwise variable selection method will be used to build the multivariable models. Multicollinearity and interaction terms of the final model will be checked, and heteroscedasticity. The model fit will be checked and assessed using Hosmer-Leme show goodness of fit test. In secondary analysis, mixed effect generalized linear models will be used to explore the changes in outcomes across time as well as the factors predicting the outcome of interest. Mediation analyses will also be conducted to explore the potential mediating psychosocial factors between predictors with clinical outcomes. Structural equation modelling (SEM) cross lagged analysis, an analytical strategy used to describe reciprocal relationships or directional influences, between variables over time, will be used to estimate the directional effects of various psychosocial factors at different time points. Statistical significance will be denoted as *p* < 0.05.

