## Methodology

### Study design

The Singapore KneE OA CoHort (SKETCH) study is a multi-centre, prospective cohort study. The reporting of the study will follow the Strengthening the Reporting of Observational Studies in Epidemiology (STROBE) guidelines [23]. The Prognostic Research Strategy (PROGRESS) framework was used to incorporate best practices for prognostic research as part of this study protocol [24].

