### Sample size calculation

Sample size was estimated using G*Power 3.1.9.2. With a small effect size of 0.05, 0.05 type I error, 0.95 power of study and 10 predictive factors to be included into the model, the study will need to recruit 262 subjects. The final estimated sample size will be 420 cases after considering 20% attrition rate at each time point [(262 × 0.2) × 3 + 262] up to 2 years. Recruitment will be continued through the entire period to maximize statistical power.

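### Univariable screening plus stepwise selection read at p<0.05 gives invalid p-values and is not the fixed 10-factor model that the 262 was calculated for

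*Protocol article*

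**What the plan says.** The primary aim (Study aims) is to identify the critical psychosocial factors that prognosticate outcome in knee OA. The section on prognostic factors sets out the analysis for knee function in two data-driven steps. First, "Simple linear regression will be used to explore the variables which significantly predict the outcome". Then a "stepwise variable selection method will be used to build the multivariable models". The same section sets significance at p<0.05. It states neither the direction of the stepwise procedure nor its entry and removal thresholds, and it does not name the factors.

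The sample size section describes something different: "With a small effect size of 0.05, 0.05 type I error, 0.95 power of study and 10 predictive factors", and continues with "10 predictive factors to be included into the model, the study will need to recruit 262 subjects". That is a model whose ten members are known in advance. Under Study design, the article says that a prognosis-research "framework was used to incorporate best practices for prognostic research as part of this study protocol".

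**The concern.** The selection step produces the answer to the primary aim: whatever survives it will be reported as a critical factor. A p-value for a variable chosen because its p-value was small no longer has its nominal error rate, and the coefficient of a weak variable that passes the threshold tends to be too large. The stated power also cannot be carried over, because it belongs to a test of a coefficient named beforehand. The discussion section intends the results to identify high-risk groups and shape care models, so a falsely named factor, or a weak one that looks strong, could be acted on.

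**Working it through.** **1. Reproduce 262.** Inputs from the sample size section: effect size 0.05, alpha 0.05, power 0.95, 10 predictors. The article does not name the metric; I take it as G*Power's f². Noncentral F with λ = f²·N and denominator df = N − p − 1:

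- One coefficient (numerator df 1, p = 10): power 0.9494 at N = 261 and 0.9501 at N = 262. This matches the stated figure exactly.
- Readings that do not match: one-sided single coefficient, 218; 0.05 read as R², 249; overall test of all 10 predictors, 497.

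So 262 powers one coefficient, two-sided, unadjusted. With Bonferroni over 10 (alpha 0.05/10 = 0.005), power at 262 is 0.783, and 0.95 needs N = 401. Model size alone costs almost nothing: one coefficient in a fixed 23-predictor model needs 263.

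**2. Count the candidates.** From the baseline section and Tables 2 and 3:

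- 8 sociodemographic items;
- 2 arthritis-status variables (symptom duration, Kellgren-Lawrence grade);
- 3 indices (Charlson, Barthel, Parker);
- 10 psychosocial scales (nine in Table 2, plus the two-item pain acceptance scale in Table 3).

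8 + 2 + 3 + 10 = 23, before dummy coding. That all 23 enter the screen is an assumption.

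**3. Upper figure for false selection.** If no candidate is prognostic and all are independent, P(at least one false) = 1 − 0.95^m:

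- m = 23: 69.3%
- m = 10 (psychosocial only): 40.1%
- m = 14: 51.2%; m = 13: 48.7%

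If the phase footnotes to Table 2 mean that a participant lacks the two phase-2 scales or the three phase-1 scales, m is 21 or 20 in total (65.9% or 64.2%) and 8 or 7 for psychosocial scales (33.7% or 30.2%).

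**4. Simulation of the two steps.** Assumptions: screen at 0.05, then backward elimination at 0.05; 23 normal candidates with pairwise correlation 0 or 0.3; unit residual variance; 1,500 studies per setting. The sample sizes are 262, 420 (no loss) and 215 (420 × 0.8³ = 215.04, three compounded 20% losses). An effect of 0.15 SD is f² = 0.0225, and 0.22 SD is f² = 0.0484, close to the design value (both somewhat less when candidates are correlated). Cells show correlation 0 / 0.3.

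| n | True effects | Any false factor | False psychosocial factor | Overstatement of retained true effects |
|---|---|---|---|---|
| 215 | none | 68% / 57% | 37% / 26% | – |
| 215 | three of 0.15 SD | 54% / 56% | 27% / 23% | 32% / 42% |
| 215 | three of 0.22 SD | 52% / 44% | 25% / 21% | 7% / 11% |
| 262 | none | 68% / 59% | 38% / 28% | – |
| 262 | three of 0.15 SD | 53% / 52% | 26% / 25% | 24% / 33% |
| 262 | three of 0.22 SD | 48% / 42% | 23% / 20% | 5% / 7% |
| 420 | none | 69% / 59% | 37% / 27% | – |
| 420 | three of 0.15 SD | 56% / 48% | 28% / 22% | 9% / 13% |
| 420 | three of 0.22 SD | 49% / 51% | 25% / 27% | 0% / 0% |

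Repeat runs move entries by a few points; the overstatement of 0.15 SD effects at n = 215 came out at 33–43% in one. A forward stepwise variant at n = 262, with 3 to 10 true effects of partial f² = 0.05, gave 25–49% for any false factor. Another set with three or five true effects gave 41–64%. Roughly 25–60% summarises these.

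**The case against.** A fair defence has several parts.

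- **Exploratory purpose.** The abstract words the aim as exploring psychosocial factors, and an observational cohort may generate hypotheses. This stands as far as an exploratory label would answer much of the concern. But the study aims speak of identifying critical factors, and the analysis section carries no such label.
- **Unstated details.** Direction, thresholds and the exact pool may sit in a fuller plan. This stands too: the percentages rest on my assumptions. The choice of screening plus stepwise selection is nevertheless stated, and no choice of thresholds turns it into a fixed 10-factor model.
- **The stronger reading.** A reader might infer that the procedure will name false critical factors more often than not. The documents do not support that. The 69% needs all 23 candidates to be null and independent, and it counts age, housing and comorbidity alongside the scales that the aim concerns. For psychosocial factors the rate stayed below one half in every setting tried.
- **Coverage.** It is tempting to say that intervals for retained terms cover only 62–79%. That mostly repeats the false-selection rate, because a null term kept at p<0.05 cannot cover zero. Retained true terms covered about 92–98%.
- **Overall power.** The power of 0.67 at 262 for an overall 10-predictor test is not evidence against the plan, because no such test is planned.
- **Imputation.** Separate selection in each imputed dataset can yield different models, but methods exist to combine selection with multiple imputation, and the article imputes only where appropriate. This is a complication, not an impossibility.

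**Conclusion.** The point holds in a limited form. Two parts do not depend on simulation: p-values read at 0.05 after screening and stepwise selection are not valid, and the 0.95 power belongs to one pre-named coefficient in a fixed 10-predictor model at unadjusted alpha, not to the analysis described.

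The size is conditional on 23 candidates and thresholds of 0.05:

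- If nothing is prognostic, the chance of at least one false factor is up to about 69% for any factor and 40% for a psychosocial one.
- If some factors are prognostic, it is roughly 25–60% for any factor and, with three true effects, about 16–28% for a psychosocial one.
- Overstatement matters mainly for weak effects: about 9–43% at 0.15 SD depending on n, against about 0–11% near the design f² of 0.05.

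The true effects and correlations are assumed, not taken from the article.

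**What to change.** - Drop the univariable screen and the stepwise selection.
- Name in advance the psychosocial factors and the adjustment covariates, and keep all of them in the model. Limit the psychosocial set to scales given to the same participants: the phase footnotes to Table 2 may rule out one model with all ten, and this must be settled first.
- State the time point to which the model applies.
- Fit that same model in each imputed dataset and pool. Report every coefficient with its interval.
- Control multiplicity across the psychosocial coefficients (Holm or false discovery rate), or label the findings exploratory.
- If a reduced model is also wanted, use a penalised fit with bootstrap optimism correction and label it exploratory.
- Restate the 0.95 power as power for a single coefficient at unadjusted alpha 0.05. If Bonferroni over 10 is adopted, give the corresponding figure (0.78 at 262).

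The cost is a change of wording and some analysis time, with no new data. Intervals will be somewhat wider and fewer factors will be called significant.

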#### Clinical, productivity and healthcare utilization outcomes

Recommendations set out by the OA Research Society International (OARSI) for domains of interest pertaining to non-surgical management of OA were adopted (i.e., pain, physical function, activity level, global assessment, and quality of life, etc.) [34, 35] for the clinical outcomes. The primary outcome will be Knee OA and Outcomes Score-12 (KOOS-12) [36]. The KOOS score has previously been validated in Singapore [37]. Other domains include quality of life, global assessment and symptom satisfaction (Tables 2 and 3).

**Table 2 Tab2:** Overview of outcome measures

Baseline Characteristics	Psychosocial Variables		Clinical, Productivity and Healthcare Utilization Outcomes	
**Sociodemographic**	**Depression and Anxiety**	Patient Health Questionnaire-4	**Knee Function**	Knee OA and Outcome Score (KOOS)
**Arthritis status**	**Pain catastrophizing/ fear of movement**	Brief fear of movement	**Quality of Life**	EQ-5D
**Comorbidities and Functional Status**	**Pain experience**	Pain intensity and interference PEG Scale	**Physical Performance**	Gait Speed Time-up-and-Go (TUG) Sit-to-stand (STS) Stair climb
	**Social support**	Multidimensional Scale of Perceived Social Support	**Physical Activity Level**	Step count UCLA activity level
	**Built Environment**^a^	Built environment questionnaire	**Dietary behaviour**	Dietary Questionnaire
	**Chronic Illness Shame**^a^	Chronic Illness Shame Scale	**Global assessment**	Global Perceived Effect
	**Religion and Spirituality**^a^	Religion questionnaire	**Symptom Satisfaction**	Patient Acceptable Symptom Scale
	**Injustice experience**^b^	Injustice Experience Questionnaire	**Cost, Productivity and Healthcare Utilization**	OA Cost and Consequences Questionnaire (including indirect costs and productivity)
	**Self-efficacy**^b^	Arthritis Self-Efficacy Scale	**OA Care Quality**^a^	OA Quality Indicator (OA-QI)

^a^To be administered in phase 1 of study

^b^To be administered in phase 2 of study

**Table 3 Tab3:** Outcome measures

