**2. Knee function**	
** KOOS-12**	KOOS-12 is a 12-item assessment tool on the participants’ perception of their knee function in the domains of pain, function and daily living, and quality of life [36]. It is measured on a 5-point Likert scale from 0 to 4, with 4 questions in each domain and scored using summative scores in each domain
** Physical Performance**	4 physical performance activities encompass the key domains of functional activities 1. Gait speed 2. Timed up-and-go 3. 4-stair climb test 4. 30-s chair stand

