#### Handling of missing data

The missing data percentage will be explored and addressed when appropriate. Logistic regression will be used to ascertain the missing data mechanism and the association between the missingness and baseline covariates. Where appropriate, multiple imputation with predictive mean matching (PMM) will be used to predict and impute the missing continuous data based on the observed baseline covariates at each follow-up. On the other hand, the imputation of binary outcomes will be done using the ‘miimputelogit’ package from STATA [57].

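### The only goodness-of-fit test named for the linear KOOS-12 model is Hosmer-Lemeshow, which needs a binary outcome and so is not valid for that model

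*Protocol article*

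**What the plan says.** All references are to the protocol article.

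- **Outcome.** The section on clinical, productivity and healthcare utilization outcomes makes KOOS-12 primary. Table 3, under knee function, describes its scoring: "It is measured on a 5-point Likert scale from 0 to 4, with 4 questions in each domain and scored using summative scores".
- **Model.** The section on prognostic factors begins: "Linear regression modelling will be used to investigate the factors that influence the knee function of the patients". Simple linear regressions come first, then multivariable models built by stepwise selection.
- **Diagnostics.** Two sentences follow in order. The first is "Multicollinearity and interaction terms of the final model will be checked, and heteroscedasticity". The second is "The model fit will be checked and assessed using Hosmer-Leme show goodness of fit test" (the break inside the test's name comes from text extraction and is not a defect).
- **Other models.** Only after that does the text move on: "In secondary analysis, mixed effect generalized linear models will be used to explore the changes in outcomes across time". Mediation analysis and structural equation models come next.
- **Logistic regression.** It is named under the handling of missing data, for a different purpose: "Logistic regression will be used to ascertain the missing data mechanism and the association between the missingness and baseline covariates". The same section imputes binary outcomes with a logit method. No logistic model of an outcome is specified.

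**The concern.** The fit-test sentence stands directly after the linear-model text and before the secondary analyses, so by position it governs the linear regression of knee function. The test it names belongs to models of a binary outcome.

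What is at stake is the check of model specification. The primary aim is to identify psychosocial factors that predict outcome. Most of those factors are questionnaire totals, entered against an outcome that is itself a bounded score. If a factor's relation to KOOS-12 is curved, a straight-line term can misstate its association or make it look unimportant. A fit assessment should reveal that, and the one named cannot be carried out on this model.

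**Working it through.** **1. Which model the test applies to.**

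| Element | What the article gives | Section |
|---|---|---|
| Outcome | KOOS-12: 4 items per domain, each 0 to 4 | Table 3, knee function |
| Model | Linear regression | Prognostic factors |
| Named fit test | Hosmer-Lemeshow | Prognostic factors, before the secondary analyses |
| Logistic regression | Missingness only (plus logit imputation) | Handling of missing data |

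Each domain runs from 4 × 0 = 0 to 4 × 4 = 16. Table 3 also lists physical performance tests under knee function (gait speed, timed up-and-go, stair climb, chair stand). These are speeds, times or counts, so the wider reading of knee function brings in no binary outcome either.

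**2. Cross-check that the primary model is linear.** The sample size section uses "With a small effect size of 0.05, 0.05 type I error, 0.95 power of study and 10 predictive factors to be included into the model" and arrives at 262. Take 0.05 as Cohen's f² (an assumption) and test one coefficient, two-sided, among 10 predictors. The noncentrality is λ = f² × N = 0.05 × 262 = 13.1, with 262 − 10 − 1 = 251 error degrees of freedom. Power is 0.9501, so 262 is reproduced. The attrition formula gives 262 × 0.2 × 3 + 262 = 419.2, in line with the stated 420. The planning figure is therefore a linear-regression figure. Nothing below depends on it except the illustrative n = 262.

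**3. The statistic on the planned outcome.** Hosmer-Lemeshow sums, over groups of fitted probability π,

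(O − E)² / [n π (1 − π)].

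It needs π between 0 and 1. Putting fitted scores in its place:

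- domain score of 8 on 0 to 16: 8 × (1 − 8) = −56
- score of 50, if a 0 to 100 scale were used (assumed): 50 × (1 − 50) = −2450

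The denominator is negative, so the statistic is undefined for this outcome.

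**4. What if the score were rescaled to 0 to 1 and the test forced?** This is an illustration on assumed inputs: n = 262, one standard-normal predictor with slope 0.06, 10 groups, chi-square on 8 df, 2000 runs per setting, and a straight-line fit that omits a quadratic term q(x² − 1).

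| Residual SD | q = 0 (model correct) | q = 0.05 | q = 0.08 |
|---|---|---|---|
| 0.15 | 0% rejected | 0% | 4.6% |
| 0.20 | 0% rejected | 0% | 8.8% |

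The binomial variance is the reason. At a mean of 0.5 it is 0.5 × 0.5 = 0.25 per patient, whereas the actual residual variance is 0.15² = 0.0225 or 0.20² = 0.04. The ratios are 0.09 and 0.16, so the noise part of the statistic is shrunk to between about a tenth and a sixth of what the reference distribution expects.

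The omitted curvature is not small. At two SDs, q = 0.05 displaces the outcome by 0.05 × (4 − 1) = 0.15 of the whole scale, and q = 0.08 by 0.24. An ordinary t test of the squared term has noncentrality of about q × √(2n) / SD, since x² − 1 has variance 2. For q = 0.05 this is 0.05 × √524 / 0.20 = 5.7, or 0.05 × √524 / 0.15 = 7.6, against a critical value near 2. A functional-form check would almost always find curvature that the forced test misses.

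**5. What the other planned checks cover.** Heteroscedasticity concerns residual variance, multicollinearity concerns overlap among predictors, and interactions concern whether effects depend on one another. None asks whether each continuous predictor enters in the right form. The general analysis section also plans skewness, kurtosis and histograms of continuous data. Those describe the variables themselves, not the fitted model.

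**The case against.** **The test was meant for binary outcomes and was misplaced when the text was condensed.** This is possible. The symptom-acceptability item and the treatment-failure item are yes/no, and the article speaks of multivariable models in the plural. But no logistic outcome model is specified anywhere, and the sentence sits within the linear-model text. If this was the intention, the article has to say so, and the linear model would then have no named goodness-of-fit assessment.

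**Valid diagnostics are already planned.** This stands. A reader might infer that the primary model has no valid check at all. The article does not support that, because the preceding sentence commits to heteroscedasticity, multicollinearity and interaction checks. Nor would a marked ceiling on KOOS-12 necessarily go unnoticed, since the planned histograms and skewness could show it.

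**An analyst would notice and use ordinary linear diagnostics.** This is likely, and it keeps the practical harm small. A reader might also infer that KOOS-12 would be dichotomised to make the test run. Nothing in the article proposes that; Table 3 keeps summed domain scores.

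**Stepwise over-fitting is the larger danger.** A reader might count over-optimistic R2 after stepwise selection against this sentence. It does not belong here: no in-sample goodness-of-fit test, correct or not, is designed to detect that optimism.

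**The full analysis plan may cover it.** That would answer an omission. Here the article states a specific test that does not fit the model it names.

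**Conclusion.** The point holds in this limited form: the only goodness-of-fit test named for the linear model of KOOS-12 is not valid for that model, and the valid checks planned beside it do not assess linearity or functional form.

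The size is modest. The sentence concerns diagnostics; it does not alter how the coefficients are computed, and it leaves the sample size of 262, inflated to 420, unaffected.

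The conclusion rests on two readings of the text: that the fit-test sentence refers to the linear model it follows, and that knee function is analysed as a score, as the linear model and Table 3 indicate. The simulated rejection rates rest on assumed effect sizes and residual SDs. They illustrate the mismatch and are not needed for the conclusion.

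**What to change.** Replace the fit-test sentence so that it says:

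- The fit of the linear models will be assessed by residual-versus-fitted and Q-Q plots, by a functional-form check (for example RESET, or spline terms for continuous psychosocial scores), and by adjusted R2 or a plot of observed against predicted KOOS-12.
- Hosmer-Lemeshow will be used only for any logistic models of binary outcomes, such as symptom acceptability or treatment failure, and those models will be named.

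The planned heteroscedasticity, multicollinearity and interaction checks stay as they are. The cost is one sentence and a few lines of extra analysis code, with no change to data collection or sample size.

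### The leading KOOS-12 regression takes one visit at a time and imputes from baseline covariates only, so dropouts' earlier follow-up scores do not inform the long-term estimate; the planned mixed model would use them

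*Protocol article*

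**What the plan says.** In the Protocol article, the section Prognostic factors that influence the rehabilitation outcomes opens with the main model: "Linear regression modelling will be used to investigate the factors that influence the knee function of the patients". Simple regressions come first, then stepwise selection. The model for repeated scores follows: "In secondary analysis, mixed effect generalized linear models will be used to explore the changes in outcomes across time". That sentence goes on to give the mixed models a second job, finding predictors of the outcome. A cross-lagged structural equation model across time points is also planned. The protocol does not call the linear regression primary; its rank follows from its place and from the word secondary attached to the mixed models.

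Other sections set the context:
- Study aims: prognosis over both the short and the long term.
- Clinical, productivity and healthcare utilization outcomes: KOOS-12 is the primary outcome.
- Table 4: knee function at baseline, 4, 12 and 24 months.
- Sample size calculation: 262 subjects, raised to 420 after "considering 20% attrition rate at each time point".
- Handling of missing data: multiple imputation where appropriate, with continuous follow-up values imputed from baseline covariates.

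**The concern.** An ordinary regression takes one outcome value per patient. Fitted at a late visit, it sees only the patients measured there plus any imputed values. A patient who gives scores at 4 and 12 months and then leaves has supplied what are probably the best available predictors of the missing 24-month score. Neither the regression nor the imputation model uses them.

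Two things are at stake. One is precision at the late visit, where expected loss is greatest. The other is bias: if patients leave because of how they scored at an earlier follow-up visit, neither a completer regression nor imputation from baseline covariates alone fully accounts for it. A likelihood-based model of all follow-up scores does, provided dropout depends only on what has been observed.

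**Working it through.** **1. The protocol's own figures.** The inputs are "With a small effect size of 0.05, 0.05 type I error, 0.95 power of study" and "10 predictive factors to be included into the model". Read 0.05 as Cohen's f² and test one coefficient two-sided with N − 11 degrees of freedom and noncentrality √(0.05·N). The smallest N with power 0.95 is then 262 (power 0.9501), as stated. A one-sided test would need 218, and a joint test of all ten factors 497. The inflation also reproduces: 262 + 3 × (0.2 × 262) = 419.2, stated as 420. The sample size therefore rests on one coefficient in a single-outcome regression.

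**2. Patients left at 24 months.** There are two readings of the attrition rate.
- Compounding: 420 × 0.8 = 336, × 0.8 = 268.8, × 0.8 = 215. Regression on 215 has power 0.904.
- Additive, as in the protocol's formula: 420 − 157.2 = 262.8. Regression on these has power of about 0.95.

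**3. Gain from the repeated-measures model.** Assume patients who leave do not return, an effect specific to each visit, and unit residual variance. Let n₁, n₂, n₃ be the numbers at 4, 12 and 24 months, ρ₁₃ the residual correlation of 4 with 24 months, and R² the squared multiple correlation of the 24-month score on the two earlier ones. The large-sample variance of the 24-month coefficient is proportional to

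V = (1 − R²)/n₃ + (R² − ρ₁₃²)/n₂ + ρ₁₃²/n₁,

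against 1/n₃ for regression on completers. The effective N is 1/V. With equal correlations ρ (exchangeable), R² = 2ρ²/(1 + ρ) and ρ₁₃ = ρ. With first-order autoregressive correlations, R² = ρ² and ρ₁₃ = ρ².

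The between-visit correlation is not in the protocol; 0.3–0.8 is an assumed range. Example, exchangeable 0.5, compounding loss: 0.6667/215.04 + 0.0833/268.8 + 0.25/336 = 0.004154, so effective N = 241 and the gain is 241/215 − 1 = 12%.

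| ρ | Pattern | Effective N | Gain | Power |
|---|---|---|---|---|
| 0.3 | autoregressive | 219 | 2% | 0.909 |
| 0.3 | exchangeable | 224 | 4% | 0.915 |
| 0.5 | autoregressive | 229 | 6% | 0.919 |
| 0.5 | exchangeable | 241 | 12% | 0.932 |
| 0.7 | autoregressive | 249 | 16% | 0.940 |
| 0.7 | exchangeable | 267 | 24% | 0.953 |
| 0.8 | autoregressive | 267 | 24% | 0.953 |
| 0.8 | exchangeable | 285 | 32% | 0.964 |

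Simulation of 3,000 cohorts per setting gave 12%, 17%, 24% and 33% for correlations 0.5, 0.6, 0.7 and 0.8, in line with the exchangeable rows.

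**4. What changes the size.**
- *No dropout.* With n₁ = n₂ = n₃, V = 1/n₃, so the gain is zero. At 4 months there is no earlier follow-up score to borrow, so the gain is zero there too.
- *Baseline KOOS-12 as a covariate.* Exchangeable raw correlation r becomes r/(1 + r), so 0.3–0.8 becomes 0.23–0.44 and the gain 3–9%. Under the autoregressive pattern the residual covariance of visits j < k is r^(k−j) − r^(j+k). The gain is then 2% at 0.3, 6% at 0.5, 12% at 0.7 and 16% at 0.8. Six of these eight settings lie at about 2–9%.
- *Additive attrition.* The variance ratio is 0.98–0.81, and power moves from about 0.95 to 0.954–0.981.

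**5. Bias.** With dropout driven by the previous score (assumed logit slope 0.5 per SD), the completer coefficient was 3–6% too small in simulation and the repeated-measures coefficient was essentially unbiased. At f² = 0.05 the coefficient is about √0.05 = 0.224 residual SD, so the bias is 0.007–0.013. Against a standard error near 0.07 that is 0.1–0.2 of a standard error.

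**The case against.** The strongest reply is that regression on baseline factors at a fixed horizon is a legitimate prognostic analysis, and that the choice lies between two valid methods. That stands: nothing here contradicts another part of the protocol or misstates a figure.

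A reader might go further and infer that the other visits' data are thrown away. They are not. The secondary mixed models also look for predictors and use all visits, and so does the cross-lagged model.

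A reader might also infer that the choice of model leaves the study short of its planned power. It does not. The fall to 0.90 comes from compounding the attrition that the protocol adds up; on the protocol's own arithmetic the regression keeps about 0.95. That is a sample-size matter, separate from this point.

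Imputation is planned, so a pure completer regression is not exactly the analysis described, and baseline KOOS-12 could enter the imputation. This narrows the gap but does not close it, because follow-up scores are still left out.

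Power of about 0.99 for an effect averaged over the three visits is no fair comparison. It answers a different question, and precision of that order at 24 months would need the same effect at every visit.

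**Conclusion.** The point holds as a matter of efficiency and robustness. In the leading analysis, the follow-up scores of patients who later drop out do not inform the long-term estimate, and the planned imputation does not bring them in. The cost at 24 months is 2–32% of efficiency under compounding loss. Most settings give single figures once baseline KOOS-12 is in the model, and with complete data there is no cost. The bias is small under the assumed dropout model.

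These sizes rest on three things the protocol does not give: the between-visit correlation, 24 months as the visit of interest, and compounding attrition. The direction does not depend on them: with a correctly specified covariance the repeated-measures model is, in large samples, at least as precise as the completer regression and tolerates dropout that depends on earlier observed scores. The documents do not support a claim of lost data, an underpowered design caused by this choice, or serious bias.

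**What to change.** Make the already planned mixed model the primary KOOS-12 analysis: the 4-, 12- and 24-month scores as outcomes, with visit, factor and factor-by-visit terms and an unstructured covariance. Read the short- and long-term effects from that one model, which also settles which visits the prognostic statements refer to. Keep the single-visit linear regressions as sensitivity analyses, and let any imputation for them also use earlier follow-up KOOS-12 scores.

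No new data are needed, but this is more than a swap of order. Ten factors over three visits add 10 × (3 − 1) = 20 interaction terms, there is more model checking, and the stepwise selection step must be respecified for the mixed model.
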